## Abstract

Despite substantial progress, Bangladesh still has a high rate of maternal deaths owing to difficulties during pregnancy, delivery, and the postpartum period. Increasing facility delivery is mandatory to reach the goal of bringing down the MMR to <70 deaths/100,000 live births by 2030. In the era of digitalization, the introduction of e-registration and mHealth may aid the government in reaching this target. The southern part of Bangladesh is a hazard-prone area, where service uptake from institutions is low. This study aims to determine the effect of an e-registration tracking system and mHealth counseling on institutional deliveries to pregnant mothers in hazard-prone areas of southern Bangladesh. We will conduct an open-label, two-arm, non-randomized controlled cluster trial for six months and use three hazard-prone areas for intervention and another three hazard-prone areas for control. We will collect data at baseline and end-line of the study period using a structured questionnaire. We will enroll at least 268 pregnant mothers from the intervention and 268 pregnant mothers from the control areas after screening based on the inclusion and exclusion criteria. Pregnancy information will be obtained from the Family Welfare Assistant register. The respondents of the intervention arm will be registered in the e-Registration system, and receive voice call and text messages from the midwives to have their deliveries done in healthcare facilities. We will follow the participants until their delivery and exclude those respondents from the study who will have post-dated delivery, migrate out, lost to follow-up, or die during the study period. Random-intercept mixed-effect logistic regression will be performed to explain the relationship of e-registration and mHealth package with institutional delivery. Institutional delivery is still uncommon in Southern Bangladesh despite several interventions. Innovative approaches like e-registration and mHealth counseling may be helpful to bring women to health facilities. The findings from the study might enable the policy makers of Bangladesh to integrate the intervention package into the existing healthcare system. This experiment is registered in the open science framework.

**Clinical trial registration:** Registration number: DOI 10.17605/OSF.IO/YZE5C) and https://www.clinicaltrials.gov/ (registration number: NCT05398978.

## Introduction

The Sustainable Development Goal-3 aimed to scale down the maternal mortality ratio to below 70 deaths per one hundred thousand live births by 2030 [1]. Despite rigorous efforts across the nations worldwide, approximately 810 women die due to obstetric complications every day [2]. In response to the call and to achieve the targeted goal of SDG, the world has strengthened the traditional approaches, adopted innovative interventions, and spread out its scope to inter-sectoral involvement. Incorporating e-registration and mHealth into the maternal healthcare system is one such step that is showing promising results in both developed and developing countries [3–4].

Institutional delivery is one of the key tools to ensure safe delivery under trained medical practitioners and tackle any delivery-related complications efficiently reducing maternal deaths and thus help to reach the SDG target. According to a joint report by the World Health Organization and UNICEF, around 83% of deliveries were conducted by skilled providers worldwide during the 2014–2020 period [5]. However, the emergence of the global pandemic COVID-19 has decelerated progress to a great extent [6]. Setting up an effective tracking system and adopting a patient-centered approach to encourage the patients for facility delivery is inevitable to confirm an increase in institutional deliveries [4].

A non-randomized controlled study conducted by Solomon Shiferaw et al. in Ethiopia featured an increase of 14.7% in facility delivery compared to the control group due to implementing mHealth services using both voice calls and text messages [4]. Similar positive findings were observed in a study conducted in Tanzania by Julia D. Battle et al. [7].

Bangladesh targets to drop down Maternal Mortality Ratio (MMR) to 121 deaths per one hundred thousand live births by 2022 and below 70 deaths per one hundred thousand live births by 2030 [8, 9]. Here, 53.8% of the deliveries are conducted at the facility level, whereas the target of the Government of Bangladesh is in reaching a rate of 85% by 2030 [10, 11]. In the era of digitalization, the introduction of e-Registration and mHealth may aid the Government of Bangladesh to reach this ambitious target. A study conducted in Bangladesh on the impact of mHealth among Aponjon users has shown promising results. Among the Aponjon users, 45% chose facility delivery, whereas, among the control group, 32% chose home deliveries [3]. But the study interventions were e-Registration and mHealth using text messages only. There was no use of voice calls [3].

However, the effect of e-registration tracking and mHealth counseling in both voice calls and text messages as a package on institutional delivery in the Bangladesh country context is yet unknown. Although the study conducted in Ethiopia showed positive results in increasing the facility delivery using both text messages and voice calls, the cultural, social, and geographical variations present between the Ethiopian and the Bangladeshi population beg the importance of a separate study to be conducted in the Bangladesh country context [4]. Additionally, the Southern part of Bangladesh is a hazard-prone area, and the service uptake tendency from the institution is much lower here, about 11% lower than the national estimate [12]. Areas that are affected by natural calamities such as floods, water logging, cyclone, tornado, storm/ tidal surge, thunderstorms, river/coastal erosion, landslide, salinity, etc. are termed hazard-prone/ disaster-prone areas [13]. Among 64 districts of Bangladesh, 19 districts are listed as disaster-prone areas of Bangladesh [13]. Chandpur and Bhola districts of the Southern part of Bangladesh are on the list and according to the report of the Bangladesh Bureau of Statistics both Chandpur and Bhola are affected by the cyclone, excess rainfall, river erosion, and thunderstorm [13, 14]. According to the study conducted by Irene Lafarga Previdi et al., natural disasters adversely affect maternal health service uptake from institutions [15]. Another study conducted by Abdullah et al. in Bangladesh suggested that natural disaster lowers the use of maternal healthcare services due to restriction on service accessibility, difficulties in transportation, healthcare facilities located far from the locality, burden of service cost for the poor, and disaster-affected population, lack of service readiness of the healthcare facilities, and skilled healthcare professionals [16]. Thus, achieving the targeted institutional delivery rate is a challenge.

In Bangladesh, paper-based registers are used mostly in the health system to keep a record of health-related data of the care-receivers. The Directorate General of Family Planning (DGFP) of the Ministry of Health and Family Welfare (MoHFW) of Bangladesh uses Family Welfare Assistant (FWA) registers to keep track of pregnant mothers at the community level. Each FWA is assigned to one or more than one adjacent union who visits houses to conduct population registration, eligible couple registration, and pregnant mother registration quarterly. The data were stored in the paper-based registers previously, and union-level data were compiled monthly to produce sub-district-level reports. The field activity and data validity were checked by the Family Planning Inspectors (FPI)s. However, carrying a large register during home visits, input data in the field, and monthly compilation of the huge dataset manually was cumbersome, time-consuming, and prone to human error. To address the problems, the digitalization of the FWA register of 39 districts to an e-Register system was a step forward to initiating e-registration in Bangladesh taken by the Directorate General of Family Planning in accordance with the rest of the world [9]. This initiative has eased the registration system, decreased workload, increased efficiency, and minimized human error [17].

The Management Information System (MIS) unit, DGFP will start e-Registration in Chandpur Sadar, Kachua, and Faridganj sub-districts of Chandpur district with the technical assistance of Maternal and Child Health Division of icddr,b under the Safe Motherhood Promotion- Operations Research on Safe Motherhood and Newborn Survival (SMPNS) Project. The project aims to reduce maternal and newborn mortality by developing and evaluating intervention packages at the project implementation sites. Strengthening pregnancy registration is one of the key mandates of this project, and assisting DGFP in the roll-out of the eMIS registration system in Chandpur district was done to achieve the mandate. The project has employed midwives in the Chandpur District Hospital, Kachua Upazila Health Complex, and Faridganj Upazila Health Complex who will send text messages and make voice calls to counsel the registered pregnant mothers for institutional delivery. Therefore, we plan to conduct a two-arm, non-randomized controlled cluster trial to evaluate the joint effort of the DGFP eMIS tracking system and mHealth counseling done by the midwives in overcoming the challenge and improving institutional deliveries in the hazard-prone areas of Southern Bangladesh. We expect that e-Registration and mHealth intervention will provide policy-relevant lessons on scaling up this package to improve the facility deliveries in hazard-prone areas in Southern Bangladesh.

## Objectives of the study

The primary objective of this study is to determine the effect of e-registration and mHealth on institutional deliveries in the hazard-prone areas of Southern Bangladesh. The secondary objectives are to determine the prevalence of institutional deliveries, different modes of institutional deliveries, and the birth outcomes among mothers in these areas of Bangladesh.

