### Inclusion criteria

Pregnant mothers registered in the paper-based FWA register,Age group 19–45 years,Residence of—Intervention group: Chandpur Sadar, Faridganj, or Kachua sub-districts of Chandpur District, and Control group: Bhola Sadar, Charfesson, or Lalmohan sub-districts of Bhola District,Gestational period of 28–36 weeks,Have access to a mobile phone.

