### Exclusion criteria

Pregnant mothers with severe pregnancy-related complications at the baseline,Pregnant mothers who will develop severe pregnancy-related complications, migrate out, lost to follow-up, or die during the study period,Mothers who will deliver beyond 42 weeks of their gestational period,Pregnant mothers who will refuse to participate in the study.

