### Sample size

We have planned to recruit and then follow up a minimum of 268 pregnant mothers in the intervention areas and 268 pregnant mothers in the control areas. According to a study conducted in Ethiopia, the implementation of mHealth services using both voice calls and text messages increased facility delivery by 14.7% in the intervention group compared to the control group (43.1% compared to 28.4%; AOR: 1.98 (95%CI: 1.53, 2.55)) [4]. We decided on this proportion we need to determine the number of respondents for our study at a 5% level of error margin and 80% power. Using the formula below we determined the sample size to be 268 for each of the intervention and control groups.

$$n=\frac{p_{1}(100-p_{1})+p_{2}(100-p_{2})}{{\left(p_{1}-p_{2}\right)}^{2}}x{\left(z_{\alpha }+z_{\beta }\right)}^{2}x\;g$$

-----------------------------------------

Here,

p_1_ = 53.8% (Proportion of institutional delivery in Bangladesh) [19]

p_2_ = 68.5% (Proportion of institutional delivery following intervention assuming a 14.7% increase) [4]

z_α_ = 1.96 (at 5% error margin)

z_β_ = 0.85 (at 80% power)

g = 1.50 (design effect)

non-response rate = 5%

-----------------------------------------

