**Fig 3 pone.0271364.g003:**
[figure not shown]
Conceptual framework of data collection process.

The questionnaire is subdivided into three main sections–screening measure, baseline survey, and end-line survey. During the baseline period, we will screen pregnant mothers using the screening tools. The screening tools will include mothers who will give consent and exclude pregnant mothers with severe pregnancy-related complications, such as eclampsia, antepartum hemorrhage, sepsis, and/or COVID-19 infection. The baseline section is designed to collect data of the respondents about the socio-demographic information, pregnancy-related information, such as parity, gravida, months of pregnancy at the first antenatal visit, counseling on facility visit, birth preparedness plan, knowledge on danger signs, location, and outcome of previous pregnancy and existing comorbidities, and other information such as personal belief, social norm, choice of delivery place, health-seeking behavior in general, and the distance between the respondent’s home, and the nearest healthcare facility. It will take approximately 20 minutes to complete the baseline section of the data collection tool. The pregnant mothers will then be followed-up until their delivery. Then their delivery-related data, such as place of delivery, mode of delivery, and the delivery outcome, will be collected at the end line of the study period using the relevant section of the questionnaire, which will take about 10 minutes to fill up.

Since the baseline, the end line data collection will be done at the end of the fourth month of the study period. The baseline and end-line data collections will be done by face-to-face interviews. The questions will be read out to the participants and the data collectors will fill up the questionnaire with the information given by the mothers. The mothers who will have post-dated delivery, develop severe pregnancy-related complications, will be lost to follow-up, or die during the study period will be excluded from the study. We will exclude post-dated deliveries and mothers with severe pregnancy-related complications as, by nature of the emergence, these deliveries are conducted in the healthcare facility and do not depend on the choice of the respondent.

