### Secondary outcome

Mode of delivery

Indicator: Proportion of normal vaginal deliveries

  Proportion of cesarean sections

  Proportion of forceps and vacuum deliveries

Denominator: Total deliveries

2. Birth outcome

Indicator: Proportion of live births

  Proportion of stillbirths

Denominator: Total births

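### The secondary objective promises area-wide rates of facility delivery, delivery mode and birth outcome, but the cohort is selected, partly on the outcome itself, and cannot supply them

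*Protocol article*

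**What the plan says.** Objectives of the study sets the descriptive aim: "The secondary objectives are to determine the prevalence of institutional deliveries, different modes of institutional deliveries, and the birth outcomes among mothers in these areas". It names no narrower target population.

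The cohort is defined elsewhere:

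- **Recruitment of the participants:** women are taken from the paper-based FWA register and must consent.
- **Inclusion criteria:** "Age group 19–45 years", and "Gestational period of 28–36 weeks,Have access to a mobile phone".
- **Exclusion criteria, at entry:** "Pregnant mothers with severe pregnancy-related complications at the baseline". Data collection process gives the screening rule: "exclude pregnant mothers with severe pregnancy-related complications, such as eclampsia, antepartum hemorrhage, sepsis, and/or COVID-19 infection".
- **Exclusion criteria, after entry:** "Pregnant mothers who will develop severe pregnancy-related complications, migrate out, lost to follow-up, or die during the study period". Women who deliver after 42 weeks are also removed.

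Data collection process explains that post-dated and severe-complication deliveries are left out because they happen in a facility whatever the woman would choose. The denominators under Outcome measures and Secondary outcome are total deliveries and total births; the birth indicators include "Proportion of stillbirths". The article describes no weighting back to the areas and does not restrict the prevalence estimate to untreated women.

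**The concern.** A comparison between arms can tolerate restrictive eligibility. A prevalence estimate cannot, because its meaning depends on whom the denominator represents. Here the denominator omits women without phone access, mothers under 19, women not registered and women with severe complications. Some of these are removed because of where they deliver, which is the quantity to be estimated.

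The Discussion directs the results at government decisions on roll-out. A facility-delivery, caesarean or stillbirth rate reported for these areas would be read as a population figure when it describes a selected group.

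**Working it through.** **The plan's own figure.** Inputs from Sample size: p1 = 53.8%, p2 = 68.5%, z values 1.96 and 0.85, design effect 1.5, non-response 5%.

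- [53.8 × 46.2 + 68.5 × 31.5] / 14.7² = 4643.31 / 216.09 = 21.49
- 21.49 × (1.96 + 0.85)² = 169.67
- 169.67 × 1.5 = 254.5
- 254.5 / 0.95 = 267.9, rounded up to 268

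The stated 268 per arm reproduces and is not in question.

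**Excluding women who deliver in facilities (downward).** Let e be the share of women excluded for severe complications or post-dated delivery, and suppose that all of them deliver in a facility. The remaining cohort then shows (p − e)/(1 − e). The documents do not give e, so a range is assumed, with p = 53.8%:

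| e (assumed) | Observed rate | Shift (points) |
|---|---|---|
| 2% | 51.8/98 = 52.9% | −0.9 |
| 5% | 48.8/95 = 51.4% | −2.4 |
| 10% | 43.8/90 = 48.7% | −5.1 |
| 15% | 38.8/85 = 45.6% | −8.2 |

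The Introduction puts southern uptake about 11% below the national estimate. Read as points, the base is 42.8%, and the same range of e gives 41.6% down to 32.7%.

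**Requiring phone access (probably upward).** The documents give no figure. If 10% to 30% of women lack access and their facility rate is 10 to 20 points lower (assumptions), the estimate rises by 0.10 × 10 = 1 point to 0.30 × 20 = 6 points. This overlaps the downward range, so the net sign cannot be fixed.

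**Sampling error, for scale.** The 95% half-width for one arm is 1.96 × √(0.538 × 0.462 × 1.5 / 268) = 7.3 points. At the upper end of the assumed ranges, the selection effects approach or exceed it.

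**Pooling (conditional).** Sample size sets a "minimum of 268 pregnant mothers in the intervention areas and 268 pregnant mothers in the control areas". If the arms were combined 1:1, the plan's rates would give (53.8 + 68.5)/2 = 61.15%, which is 7.35 points above 53.8%. From a base of 42.8% the shift is also 7.35 points (50.15%).

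**Late entry and stillbirth.** A woman enters while pregnant, at any week from 28 to 36. A pregnancy that ends between 28 weeks and what would have been her entry week is never listed. Provided stillbirth is more frequent among those earlier births than among later ones (assumed), the cohort proportion understates that of all births from 28 weeks. The documents give neither the distribution of entry weeks nor the timing of stillbirths, so the size cannot be derived.

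**The case against.** The strongest reply is that this is a gap of wording in a descriptive secondary aim. The eligibility rules are published openly, the primary outcome and model do not depend on them being representative, and a careful reader can see whom the rates describe. Fig 2, which is not shown, may already account for women not enrolled. Much of this stands, and it limits the weight of the point. It does not make the objective attainable as worded.

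Several stronger readings are tempting, and the documents do not support them:

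- **That the reported prevalence will be a mixture of treated and untreated women.** No section says that the arms are pooled. Data management and analysis plan describes a chi-square comparison between groups, which needs proportions by arm. The 268 is a minimum and all listed eligible women are invited, so the ratio is not fixed at 1:1. The 7.35 points illustrate one possible analysis.
- **That nothing is known of untreated Chandpur.** The baseline questionnaire records where the previous pregnancy was delivered. That is not a concurrent rate, but it is some pre-intervention information.
- **That the facility rate will be too high.** This counts only phone access and pooling. The exclusion of facility-bound deliveries acts the other way.
- **That half of the stillbirths are missed.** With entry and events both uniform over weeks 28 to 36, half of the fetal deaths in those weeks would precede entry. Both are assumptions, and later stillbirths are still captured.
- **That the stillbirth comparison between arms is biased.** This needs the arms to differ in gestation at entry, for which there is no evidence yet.

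**Conclusion.** The point holds as a mismatch between the stated target population and the cohort. Followed as written, the plan cannot give the prevalence of facility delivery, the modes of delivery or the birth outcomes for mothers in the areas.

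The firmest part is selection on the outcome: the article removes women, before and after enrolment, for the stated reason that they deliver in facilities. On the assumptions shown (2% to 15% excluded, all delivering in a facility), that costs about 0.9 to 8.2 points from a true 53.8%. Phone access may offset it, so the net direction is unknown. Pooling would add 7.35 points, but only if it were done. The stillbirth proportion is expected to be low against all births from 28 weeks, by an unquantified amount.

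The point concerns a secondary objective. It changes neither the 268 per arm nor the primary comparison.

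**What to change.** - Reword the secondary objective so that descriptive rates are given by arm for the eligible cohort. Name the entry criteria (registered, consenting, aged 19 to 45, phone access, 28 to 36 weeks, no severe complication) and also the post-enrolment exclusions. A description that stopped at screening would still be inaccurate.
- Take usual-care rates from the control arm only, and give no single figure for the areas.
- Report how many women were left out before and after enrolment, by arm and by reason.
- Report stillbirth as a risk among pregnancies ongoing at enrolment, and show gestational week at entry by arm. The eligibility rule already requires gestation to be established. Covariate adjustment of the stillbirth comparison should not carry the fix: at an assumed 1% to 3%, 268 women yield only about 3 to 8 events per arm.

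The cost is a change of wording and a few rows in tables. The downside is a narrower descriptive claim.

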## Hypothesis

We hypothesize that e-registration and mHealth will increase institutional deliveries in the hazard-prone areas of Southern Bangladesh.

## Materials and methods

We used the SPIRIT checklist when writing this manuscript and the standard protocol items are shown in **Fig 1**.

**Fig 1 pone.0271364.g001:**
[figure not shown]
Standard Protocol Items: Recommendations for Interventional Trials (SPIRIT) checklist.

### Study design and setting

The study will be an open-label two-arm non-randomized controlled cluster trial for six months where Chandpur Sadar, Kachua, and Faridganj sub-districts will be the intervention arm as MIS unit; DGFP will initiate the eMIS registration system in these three sub-districts of Chandpur district. Chandpur is a district under the Chattogram division, located in the Southern part of Bangladesh, and is a disaster-prone area. There are 14 unions in Chandpur Sadar, 12 in Kachua, and 15 in the Faridganj sub-districts of Chandpur [18]. The Government of Bangladesh has taken the initiative to implement various models in different districts, such as the Maternal, Newborn, and Child Survival (MNCS) and Maternal, Newborn and Child Health (MNCH) project by UNICEF; Maternal, Newborn Health Initiative (MNHI) through joint UN initiatives; and USAID supported program MaMoni. But none has chosen Chandpur district as their project implementation site. Again, the majority of the social and health indicators of Chandpur Sadar, Faridganj, and Kachua sub-districts are below national estimates mostly due to the hazard-prone nature of these areas [18]. So, we have chosen these three sub-districts of Chandpur district as intervention areas. The e-registration and mHealth services are not available in Bhola District. In addition, Bhola is likely to be similar to Chandpur, especially in terms of its geographical location, susceptibility to disasters, and health care and care-seeking practices of the inhabitants [18]. So, we have selected the Bhola Sadar, Charfesson, and Lalmohan sub-districts of the Bhola district as the control arm. Bhola Sadar has 13 unions, Charfesson has 14 unions, and Lalmohan has 9 unions [19]. Unions will be considered as cluster units, and individual study participants will be the sample unit.

